### 3.1 Dose limiting toxicity (DLT)

Dose limiting toxicity (DLT) is evaluated within 42 days after administration of RRG-003 according to Common Terminology Criteria for Adverse Events, NCI-CTCAE V5.0. DLT is defined as hematologic toxicity  $\geq$  grade 4, nonhematologic toxicity  $\geq$  grade 3, or aural toxicity in grade 2 or 3 within 6 weeks. Aural toxicity was listed as follow:

| Adverse Events               | Grade 2 ear adverse events                                                                                  | Grade 3 ear adverse events                                                                              |
|------------------------------|-------------------------------------------------------------------------------------------------------------|---------------------------------------------------------------------------------------------------------|
| Ear pain                     | Moderate pain; limiting instrumental Activities of Daily Living (ADL)                                       | Severe pain; limiting self care ADL                                                                     |
| External ear pain            | Moderate pain; limiting instrumental ADL                                                                    | Severe pain; limiting self care ADL                                                                     |
| Hearing impaired (Pediatric) | Pediatric (on a 1, 2, 3, 4, 6, and 8 kHz audiogram):
Threshold shift >20 dB at 4 kHz in at least one ear | Pediatric (on a 1, 2, 3, 4, 6, and 8 kHz audiogram):
Hearing loss sufficient to indicate therapeutic |

|                                                |                                                                                                                                 |                                                                                                                                                                                                         |
|------------------------------------------------|---------------------------------------------------------------------------------------------------------------------------------|---------------------------------------------------------------------------------------------------------------------------------------------------------------------------------------------------------|
|                                                |                                                                                                                                 | intervention, including

hearing aids; threshold shift

>20 dB at 2 to < 4 kHz in at

least one ear                                                                                   |
| Middle ear inflammation                        | Serous otitis, medical

intervention indicated                                                                            | Mastoiditis; necrosis of canal

soft tissue or bone                                                                                                                                               |
| Tinnitus                                       | Moderate pain; limiting

instrumental ADL                                                                                 | Severe pain; limiting self care

ADL                                                                                                                                                              |
| Vertigo                                        | Moderate pain; limiting

instrumental ADL                                                                                 | Severe pain; limiting self care

ADL                                                                                                                                                              |
| Vestibular disorder                            | Moderate pain; limiting

instrumental ADL                                                                                 | Severe pain; limiting self care

ADL                                                                                                                                                              |
| Ear and labyrinth disorders-
Other, specify | Moderate; minimal, local or

noninvasive intervention

indicated; limiting age-

appropriate instrumental ADL | Severe or medically significant

but not immediately life-

threatening; hospitalization or

prolongation of existing

hospitalization indicated;

limiting self-care ADL |
| Otitis externa                                 | Oral intervention indicated

(e.g., antibiotic, antifungal, or

antiviral)                                          | IV antibiotic, antifungal, or

antiviral intervention

indicated; invasive

intervention indicated                                                                                    |
| Otitis media                                   | Localized; oral intervention

indicated (e.g., antibiotic,

antifungal, or antiviral)                               | IV antibiotic, antifungal, or

antiviral intervention

indicated; invasive

intervention indicated                                                                                    |

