The *OTOF* gene contains 48 exons and encodes the otoferlin which consists of 1997 amino acids, which mainly expresses in inner hair cells. The length of the *OTOF* sequence is approximately 6 kb, which together with the gene regulatory elements is longer than 7.5 kb, so it is difficult to package *OTOF* into a single AAV (~4.7 kb). Therefore, the present project uses dual AAV strategies to achieve in vivo high-efficient recombination of the *OTOF* sequence and to express functional otoferlin; also mouse hair cells will be high-efficiently and safely repaired by the inner ear hair cell-specific promoter, thereby expecting to restore auditory function of patients. Compared to previous reports, we intended to use human-derived *OTOF* and a specific-targeted promoter, which is characterized by higher safety and better tissue specificity.

AAV is the most commonly used delivery vector for gene therapy. Currently, three AAV-based drugs have been listed, including Glybera, Luxturna, and Zolgensma for the treatment of lipoprotein esterase deficiency, Leber congenital amaurosis, and spinal muscular atrophy, respectively. In addition, there are hundreds of AAV-related gene therapy drugs in the development of clinical pipelines. In the present research, AAV1 was used as the delivery vector due to its high usage frequency and proven manufacturing process. Glybera, the first listed gene therapy drug, uses AAV1 as its delivery vector. The pipelines developed by the AAV1 vector have been applied in various diseases, including muscular dystrophy, liver disease, hemophilia, viral infections, heart failure, and Huntington's chorea. Also, AAV1 is able to efficiently infect the inner ear hair cells of the target tissue in this project. The segmental package of the target gene using dual AAV vectors is a solution to break the upper limit of single vector packaging.

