#### 4. Subject inclusion criteria, exclusion criteria, and suspension criteria

##### 4.1 Inclusion Criteria

8. Participants and their guardians can fully understand and voluntarily sign the informed consent of this study, willing to cooperate with follow-up at the specified time points in the trial.
9. Be able to communicate well with the researchers and comply with the requirements under the help of the guardian. For young children without mature language skills, they could cooperate and comply with the requirements under the help of guardians.
10. A proper understanding of the trial and an appropriate expectation of the benefit.
11. 1-18 years old, gender is not limited.
12. A diagnosis of DFNB9 congenital deafness was determined based on the clinical symptoms, and gene mutation analysis for the presence of either *OTOF* homozygous or bi-allelic mutations in *OTOF*.
13. Audiology inclusion criteria: Severe to complete hearing loss ( $\geq 65$  dB).
14. Satisfy the requirements for otological surgery: conditions such as middle-inner ear deformity, vestibular-cochlear nerve development abnormality, and ear inflammation, etc. are excluded through CT scan and/or MRI scan within 3 months or during screening.

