## **11. Efficacy assessment criteria, including methods for evaluating parameters, observation time, recording and analysis**

Focusing on the purpose of the study, involving the efficacy assessment must have evaluation indicators or observation indicators, including primary and secondary evaluation indicators. At the same time, corresponding evaluation standards should be established for these indicators.

**Primary indicators:** tolerability (dose-limiting toxicity, DLT) at week 6.

**Secondary indicators:** safety, preliminary efficacy.

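### The hearing row of the DLT table does not fit children with severe to complete loss: in ears near the equipment limit, the absence of a threshold-shift DLT is uninformative

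*Supplement*

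**What the plan says.** All references are to protocol v5, whose Section 15 is the analysis plan.

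- **Population (4.1).** "Audiology inclusion criteria: Severe to complete hearing loss", from 65 dB, with no upper bound.
- **DLT (3.1).** A DLT includes "aural toxicity in grade 2 or 3 within 6 weeks". In the paediatric hearing row, grade 2 is "Threshold shift >20 dB at 4 kHz in at least one ear". Grade 3 has two limbs. One is "Hearing loss sufficient to indicate therapeutic" intervention, hearing aids included. The other is a threshold shift ">20 dB at 2 to < 4 kHz in at" least one ear.
- **Role (11 and 3).** The primary indicator is "tolerability (dose-limiting toxicity, DLT) at week 6". In the 50 µL group, no DLT in 3 to 5 participants, or at most one in 6, lets the investigators extend the trial after a comprehensive evaluation.
- **DPOAE.** In Section 7 it is named at screening (7.1.3) and as a curative-effect indicator (7.3.4), but not among the safety indicators of 7.2. Section 13.8.2 lists it with the otologic examinations and says that this content includes the product's safety indicators. Section 15.2 summarises otologic examination in the Safety Analysis Set without naming DPOAE. It is absent from the DLT table and the ear grades in 13.2, and Section 11 sets no criterion for it.

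**The concern.** The primary purpose is safety and tolerability, and the treatment is injected into the cochlea. Section 13.8.1 itself expects hearing harm: mild hearing loss is among the ear reactions above 5%, and unilateral deafness among those below 5%. A worsening criterion only works if there is room to worsen. An ear with no response at maximum output has none, yet the plan has no category for an ear that cannot be assessed, so it is counted as free of a hearing DLT.

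The DLT count matters beyond the final table. It governs extension of the 50 µL group, which opens the way to double injection or 70 µL. The amendment summary also gives the absence of DLT as a reason for expanding the dose groups, the age range and the number of participants. If part of that absence comes from the measuring range, it should not be read as evidence of cochlear safety.

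**Working it through.** The plan derives no figure on this point (the 4 to 12 cases in Section 5 have no calculation behind them), so there is nothing to reproduce. The check is ceiling arithmetic, followed by an illustration.

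**Inputs from the documents.** Eligibility from 65 dB; a shift above 20 dB; the 50 µL extension rule.

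**Assumptions, none of them in the documents.** Equipment limit L of 90 to 120 dB; 5 dB test steps; the eligibility figure taken as the threshold at the test frequency; the shift measured from the pre-dose threshold; q, the true rate of DLT-sized hearing damage; f, the share of participants in whom a shift cannot be recorded.

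**1. Shift limbs.** With pre-dose threshold b, the largest recordable worsening is L − b. The criterion needs L − b > 20, that is b < L − 20. At b = L the largest recordable shift is 0 dB.

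| L (dB) | b that can score | b that cannot | Eligible steps that cannot |
|---|---|---|---|
| 90 | 65 | 70–90 | 5 of 6 |
| 100 | 65–75 | 80–100 | 5 of 8 |
| 110 | 65–85 | 90–110 | 5 of 10 |
| 120 | 65–95 | 100–120 | 5 of 12 |

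These are shares of the scale, not of children; the documents do not give the baseline distribution.

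**2. Intervention limb.** This limb is not a shift, so it has no ceiling. But a child with at least 65 dB loss can be taken to meet it before dosing. Read literally, it would make every child a DLT. Read as new loss only, in line with the 15.2 rule that a treatment-emergent event was not present before dosing, it has nothing left to detect. Either way it does not mark new damage. The ear grades in 13.2 combine the same kinds of criterion.

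**3. Effect on the 50 µL rule, hearing DLTs only.** Take 0 of 3 as a pass, and 1 of 3 as adding three more participants with a pass at no more than 1 of 6. With p = q(1 − f):

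P(pass) = (1 − p)³ + 3p(1 − p)⁵

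| q | f = 0 | f = 0.5 | f = 1 |
|---|---|---|---|
| 0.33 | 0.43 | 0.78 | 1.00 |
| 0.50 | 0.17 | 0.60 | 1.00 |

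For q = 0.33 and f = 0.5, p = 0.165, so 0.835³ + 3 × 0.165 × 0.835⁵ = 0.582 + 0.201 = 0.783.

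**4. Chance of seeing any event.** With q = 0.30, P(at least one in n) = 1 − (1 − 0.3(1 − f))ⁿ.

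| n | f = 0 | f = 0.5 | f = 0.8 | f = 1 |
|---|---|---|---|---|
| 3 | 0.66 | 0.39 | 0.17 | 0 |
| 6 | 0.88 | 0.62 | 0.31 | 0 |

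**5. DPOAE.** Section 1 says of otoferlin "which mainly expresses in inner hair cells". DPOAE reflects outer hair cells; this is general audiology, not a statement in the documents. On that basis DPOAE can be present in a deaf ear and be lost through damage, so it could inform where thresholds cannot. The plan measures it but defines no loss and does not bring it to the DLT review.

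**The case against.** The strongest reply is that a reader might infer that a clean hearing result is guaranteed, and the text does not support that. The row contains the intervention limb, which could over-fire rather than stay silent. Ears with enough range below the limit can still show the shift. The reference threshold is unstated, and a shift measured from a recovered post-dose threshold could be recorded. The wording also lets the other ear trigger the criterion, although that says nothing about damage in the injected ear. All of this stands, and it limits the point to the shift limbs in ears near the ceiling.

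A reader might also infer that tolerability as a whole is overstated. The DLT is a participant-level composite. Vertigo, vestibular disorder and the row for other ear disorders can fire in any child, extension requires a comprehensive evaluation, and the first participant's results in each dose group go to the ethics committee. The documents do not support the wider claim.

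A third inference would be that the plan ignores DPOAE for safety, or that the normal/abnormal shift tables in 15.2 are saturated. Section 13.8.2 places DPOAE among examinations that supply safety indicators, and 15.2 may cover it as otologic examination. Saturation can apply to hearing thresholds, but not to a test that may be normal at baseline. What remains is that no loss criterion exists, nothing is specified per injected ear, and there is no link to dose decisions.

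Finally, the probabilities rest on assumed inputs. That is correct; only the ceiling inequality is independent of them.

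**Conclusion.** The point holds in a limited form. The hearing row does not fit a population that starts at 65 dB and includes complete loss. If the shift is taken from the pre-dose threshold, it cannot be recorded in an injected ear within 20 dB of the equipment limit, and the intervention limb cannot distinguish new damage from the condition being treated. For those ears the absence of a threshold-shift DLT is uninformative. It is neither evidence of safety nor evidence of harm.

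The size depends on how many ears lie in that band, which the documents do not give. Under an assumed limit of 90 to 120 dB, the band takes 5 of 6 down to 5 of 12 eligible steps. The fall from 88% to 0% in the chance of seeing an event among six children, and the rise from 0.43 to 1.00 in passing the 50 µL rule at q = 0.33, show the direction and possible reach of the problem. They are illustrations, not estimates for this trial.

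**What to change.** 1. The sponsor should reconcile the hearing row of 3.1, and the ear grades in 13.2, with a population at 65 dB or worse, and state the threshold from which the shift is measured.
2. Keep the participant-level DLT count for the dose rules. Beside it, report the threshold-shift component over injected ears with enough range below the equipment limit to record a shift above 20 dB, and state the limit and the number of ears not assessable.
3. Name DPOAE in 7.2 and 15.2 as a safety result in the Safety Analysis Set. Tabulate, per injected ear, DPOAE present at baseline and absent at W6 or later where recorded, and show this with the DLT results at each dose decision.
4. Draw no conclusion that hearing toxicity is absent for ears that neither measure can assess.

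Whether loss of DPOAE should itself be a DLT is for the sponsor to decide.

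The cost is wording in the protocol and Section 15, and a smaller stated denominator for the hearing component. DPOAE is already among the planned examinations, so no new test is needed.

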#### 4. Subject inclusion criteria, exclusion criteria, and suspension criteria

##### 4.1 Inclusion Criteria

8. Participants and their guardians can fully understand and voluntarily sign the informed consent of this study, willing to cooperate with follow-up at the specified time points in the trial.
9. Be able to communicate well with the researchers and comply with the requirements under the help of the guardian. For young children without mature language skills, they could cooperate and comply with the requirements under the help of guardians.
10. A proper understanding of the trial and an appropriate expectation of the benefit.
11. 1-18 years old, gender is not limited.
12. A diagnosis of DFNB9 congenital deafness was determined based on the clinical symptoms, and gene mutation analysis for the presence of either *OTOF* homozygous or bi-allelic mutations in *OTOF*.
13. Audiology inclusion criteria: Severe to complete hearing loss ( $\geq 65$  dB).
14. Satisfy the requirements for otological surgery: conditions such as middle-inner ear deformity, vestibular-cochlear nerve development abnormality, and ear inflammation, etc. are excluded through CT scan and/or MRI scan within 3 months or during screening.

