#### 4. Subject inclusion criteria, exclusion criteria, rejection criteria and suspension criteria

##### 4.1 Inclusion Criteria

1. Participants and their guardians can fully understand and voluntarily sign the informed consent of this study, willing to cooperate with follow-up at the specified time points in the trial.
2. Be able to communicate well with the researchers and comply with the requirements under the help of the guardian. For young children without mature language skills, they could cooperate and comply with the requirements under the help of guardians.
3. A proper understanding of the trial and an appropriate expectation of the benefit.
4. 3-10 years old, gender is not limited.
5. A diagnosis of DFNB9 congenital deafness was determined based on the clinical symptoms, and gene mutation analysis for the presence of either homozygous or bi-allelic mutations in *OTOF*.
6. Audiology inclusion criteria: Severe to complete hearing loss ( $\geq 65$  dB)
7. Satisfy the requirements for otological surgery: conditions such as middle-inner ear deformity, vestibular-cochlear nerve development abnormality, and ear inflammation, etc. are excluded through CT scan and/or MRI scan within 3 months or during screening.

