## 4.2 Exclusion Criteria

16. Gene analysis does not suggest any *OTOF* mutation, or concomitant with other gene mutations causing hearing loss.
17. Other types of deafness that are not suitable for otological surgery, such as conductive deafness, mixed deafness, malformation syndrome caused by middle - inner ear dysplasia or malformed, abnormalities of vestibular nerve or cochlear nerve through CT/MRI scan within 3 months.
18. Pre-existing otological diseases that may interfere with the interpretation of study endpoints, such as: acute-chronic otitis media, Meniere's disease, acoustic neuroma or unrecovered sudden deafness, etc.
19. A history of substance abuse, any ototoxic drug treatment (such as aminoglycosides, cisplatin, loop diuretics, etc.) within 6 months, antiviral or immunization therapy within 3 months, or vaccination within 1 month.
20. A history of complex immunodeficiency, or organ transplantation.
21. Patients with severe systemic disease or active bacterial or viral infection, such as pulmonary tuberculosis, active hepatitis B or C infection, active herpes zoster infection, pancreatitis, renal

failure, or gastrointestinal ulcers.

22. Patients with contraindications to surgery or anesthesia certified by the surgeon, anesthesiologist or designee, such as an allergy to the study medication, cardiovascular or cerebrovascular accident which occurred within the past 6 months, including myocardial infarction, heart failure, angina pectoris, cerebrovascular accident or transient ischemic attack.
23. Currently participating in or planning to participate in another clinical trial involving a drug or device within 1 year, or within 5 half-lives after the last dosing in another clinical trial.
24. Bilateral ear implants (e.g., cochlear implants).
25. With > 1:2000 neutralizing antibodies against AAV1 capsid.
26. Other severe congenital diseases.
27. A clear history of neurological or psychiatric disorders, including epilepsy or dementia.
28. Patients who require long-term use of anticoagulants is required.
29. A history of radiotherapy and chemotherapy.
30. Other conditions that investigators do not consider appropriate for participating in the present clinical study.

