## **5. The number of cases required to achieve the intended purpose of the study based on statistical principles**

According to the description above, the total number of effective cases was 4-12. Two to three dose groups were set for administration, and the exploration dose was set as 30  $\mu$ L (9.0E11 vg/ear), 50  $\mu$ L (1.5E12 vg/ear), 70  $\mu$ L (2.1E12 vg/ear). The exploration age was 1-18 years old. An effective case was defined as a subject who was given drug in compliance with the protocol and was observed for 6 weeks at least. The actual number of subjects can be adjusted according to trial requirements.

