| Urinalysis                                       | X        |    |    |    |   |   |   |   |   |   |   |             |              |              |              |                |                |                |
| Blood collection                                 | X        | X  |    |    |   |   |   |   |   |   |   |             |              |              |              |                |                |                |
| Blood routine                                    | X        | X  |    |    |   |   |   |   |   |   |   |             |              |              |              |                |                |                |
| Serum Biochemistry                               | X        | X  |    |    |   |   |   |   |   |   |   |             |              |              |              |                |                |                |
| Coagulation function                             | X        | X  |    |    |   |   |   |   |   |   |   |             |              |              |              |                |                |                |
| Virology examination (HIV, HBV, HCV)             | X        |    |    |    |   |   |   |   |   |   |   |             |              |              |              |                |                |                |
| Circulating blood qPCR                           | X        |    |    |    |   |   |   |   |   |   |   |             |              |              |              |                |                |                |
| ELISA                                            | X        |    |    |    |   |   |   |   |   |   |   |             |              |              |              |                |                |                |
| Serum anti-AAV1 antibody                         | X        |    |    |    |   |   |   |   |   |   |   |             |              |              |              |                |                |                |
| 12-lead electrocardiogram (ECG)                  | X        |    |    |    |   |   |   |   |   |   |   |             |              |              |              |                |                |                |
| Chest X-ray examination                          | X        |    |    |    |   |   |   |   |   |   |   |             |              |              |              |                |                |                |

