| MRI (ear, vestibule, brain)                      | X        |    |    |    |   |   |   |   |   |   |   |             |              |              |              |                |                |                |
| Middle inner Ear CT                              | X        |    |    |    |   |   |   |   |   |   |   |             |              |              |              |                |                |                |
| Pure tone audiometry                             | X        |    |    |    |   |   |   |   |   |   |   |             |              |              |              |                |                |                |
| ABR                                              | X        |    |    |    |   |   |   |   |   |   |   |             |              |              |              |                |                |                |
| DPOAE                                            | X        |    |    |    |   |   |   |   |   |   |   |             |              |              |              |                |                |                |
| ASSR                                             | X        |    |    |    |   |   |   |   |   |   |   |             |              |              |              |                |                |                |
| Speech recognition                               | X        |    |    |    |   |   |   |   |   |   |   |             |              |              |              |                |                |                |
| Vestibular function                              | X        |    |    |    |   |   |   |   |   |   |   |             |              |              |              |                |                |                |
| Otoscopy examination                             | X        |    |    |    |   |   |   |   |   |   |   |             |              |              |              |                |                |                |
| Ear care                                         | X        |    |    |    |   |   |   |   |   |   |   |             |              |              |              |                |                |                |
| Intra-ear injection administration               | X        |    |    |    |   |   |   |   |   |   |   |             |              |              |              |                |                |                |

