##### **13.1.2 Serious Adverse Event (SAE)**

SAEs are any undesirable clinical events occurring at any dose, such as death, life-threatening, hospitalization or prolongation of hospitalization to treat AEs, persistent or significant disability, congenital anomaly or birth defect.

An adverse event should be reported to the sponsor by the research center within 24 hours if the adverse event meets one of the following criteria and is diagnosed as serious adverse event:

Death: the death of subject resulting from adverse event;

Life-threatening: in the opinion of the investigator, an adverse event is likely to result in the immediate death of the subject without medical intervention, excluding the adverse event that occurs more seriously, and already results in death;

Hospitalization: admission to the hospital that is a result of the adverse event, not including emergency or outpatient visit;

Prolongation of hospitalization: adverse event occurs during the subject's hospitalization, which leads to the prolongation of hospitalization for AE therapy;

Persistent or significant loss of function or disability: the subject is unable to perform normal daily activities. Loss of function does not include relatively minor medical events, such as headache, nausea, emesis, diarrhea, influenza and accidental trauma (e.g., sprained ankle);

Important medical event: the event may not result in immediate death, life-threatening or hospitalization, but the important medical event may jeopardize the subject and require medical or surgical intervention to prevent any of the events above (i.e., death, life-threatening, hospitalization

or prolongation of hospitalization, etc.). For example, allergic bronchospasm requiring treatment in the emergency room or at home, convulsions that do not require hospitalization, cachexia, drug dependence or substance abuse, etc.

The hospitalization due to the progression of the original disease is not considered as serious adverse event. The hospitalization resulting from elective surgery and examination or other treatments that are scheduled prior to entering into this trial, or social reasons.

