#### 4. Subject inclusion criteria, exclusion criteria and suspension criteria

Expand the range of participant's age (from 3-10 years to 1-18 years) for potential benefits of younger and older children due to no DLT occurring in treated patients.

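### Version 5.0 opens enrollment to age 18 for either sex but has no pregnancy criterion and no baseline test that would detect an unrecognized pregnancy

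*Supplement*

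**What the plan says.** Section 4.1 of v5.0 (item 11) admits participants "1-18 years old, gender is not limited", and section 5 repeats the range: "The exploration age was 1-18 years old". The same item in v2.0 read "3-10 years old, gender is not limited". The amendment summary gives the reason as "Expand the range of participant's age (from 3-10 years to 1-18 years) for potential benefits of younger and older children", citing the absence of dose-limiting toxicity in those already treated. It mentions no safeguard for participants who could be pregnant.

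Two exclusions in section 4.2 come near the subject. Item 22 covers "Patients with contraindications to surgery or anesthesia certified by the surgeon, anesthesiologist or designee"; its examples are allergy to study medication and cardiac or cerebrovascular events. Item 30 leaves other unsuitable conditions to the investigator.

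The section 7 schedule includes "Chest X-ray examination" and "Middle inner Ear CT", both marked at baseline, together with urinalysis and several blood tests. Section 6.2.2 plans intravenous dexamethasone from three days before surgery to the fifth day after it. The postoperative-care text under section 6.3 and the risk list in 13.8.2 show that surgery is under general anesthesia. Section 3 allows, in the expansion phase, a second injection in the other ear or again in the same ear.

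The only reproductive wording is in the definition of a serious adverse event in 13.1.2, which ends with "persistent or significant disability, congenital anomaly or birth defect".

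**The concern.** For children aged 3-10, a protocol can reasonably say nothing about pregnancy. Once the range reaches 18 with no limit by sex, it can include girls who have reached menarche. The eligibility list and test schedule were not revisited for that consequence.

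What is at stake is protection of the participant and a possible fetus. Followed as written, the plan could take a girl with an unrecognized pregnancy through radiological imaging, steroid, anesthesia and an AAV vector without anyone being required to establish her status. The documents give no human pregnancy data for this vector. The same holds before a second injection. If a pregnancy began during the 52 weeks of scheduled follow-up, no reporting route would bring it to notice, so the birth-defect part of the serious-event definition could not be applied reliably.

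**Working it through.** No arithmetic applies, and the plan gives no figure to reproduce. The check is a reading of every place in v5.0 where a pregnancy rule or test would normally stand.

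1. **Eligible population.** Sections 4.1 (item 11) and 5 agree on 1-18 years and either sex. v2.0 had 3-10 years. The question therefore arises with v5.0.
2. **Inclusion criteria (4.1, items 8-14).** 0 of 7 mention pregnancy, childbearing potential or contraception.
3. **Exclusion criteria (4.2, items 16-30).** 0 of 15 mention them. In substance the list is that of v2.0.
4. **Suspension criteria (4.3, items 6-10).** 0 of 5 mention them.
5. **Schedule (section 7).** No row is a pregnancy test. The extracted table is damaged, so I rely on the row labels and not on the position of the visit marks. The labels follow the v2.0 rows in order, with four optional items added at the end: near-infrared imaging, EEG, music test and growth scale. The schedule was thus edited in this amendment, but not for this purpose.
6. **Lists outside the table.** The laboratory tests in 7.2.4, the samples in 7.5 and the safety monitoring in 13.8.2 name no pregnancy test. They agree with the table, so a row lost in extraction is an unlikely explanation.
7. **What could catch a pregnancy anyway.** Item 22 needs a contraindication that someone has identified and certified. Item 30 needs the investigator to know of the condition. The baseline medical history depends on what a minor and her guardian know and disclose. All three can act on a known pregnancy; none detects an unknown one.
8. **Monitoring.** Section 17.2.6 requires complete source verification of eligibility, but a monitor can verify only criteria that are written down.
9. **After enrollment.** Section 3 attaches no check of pregnancy status to the second injection. Section 13.6 covers the reporting of serious adverse events and does not mention pregnancy.
10. **Means already available.** Urine and blood are collected at baseline for other tests, so a pregnancy test needs no new sample.

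**The case against.** The strongest reply is that items 22 and 30 already suffice. A surgeon, an anesthesiologist and an investigator would hardly proceed with a pregnant adolescent, and few adolescents may enroll. Part of this stands. A reader might infer that a pregnant adolescent simply qualifies; the documents do not support that, because a known pregnancy can be excluded under either item. The reply does not reach the unrecognized case.

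Several stronger inferences also fail:

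- *The serious-event wording shows that the sponsor anticipated birth defects.* It does not. The same words are in v2.0, when the upper age was 10; they are generic.
- *Every participant undergoes CT.* Not certain. Item 14 accepts CT and/or MRI, done within 3 months or at screening, and the note under the schedule lets the investigator adjust examinations.
- *Participants meet a product never used in people.* The amendment summary refers to patients already treated before v5.0.
- *One pregnancy would stop the trial or distort its main result.* Section 10 contains no pregnancy rule, and the primary indicator is dose-limiting toxicity at week 6, defined by toxicity grades. Pregnancy is not itself such a toxicity.
- *The share of the age range after menarche measures the risk.* It does not. That would presume even enrollment across ages, and being post-menarchal is not being pregnant.

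The consent pages are not shown and the investigator's brochure is not part of the documents. Either may address pregnancy, but neither replaces an eligibility criterion or a scheduled test in the protocol, and both of those sections are shown.

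**Conclusion.** The gap is real and arises with v5.0: the age range was widened to 18 for either sex, and eligibility, baseline testing, re-dosing and follow-up reporting are all silent on pregnancy. A known pregnancy can be excluded at discretion; an unrecognized one would not be detected before imaging, steroid, anesthesia and vector.

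The conclusion assumes only that some girls within the permitted range have reached menarche. How many would enroll among the 4-12 effective cases is unknown, and I give no number. The affected group is probably small, but the possible harm to one participant is serious and prevention is cheap. This should be corrected for participant protection. It has no bearing on the endpoints, the sample size or the analysis.

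**What to change.** - **Section 4.2:** add pregnancy as an explicit exclusion.
- **Section 7 schedule:** add a baseline row for a pregnancy test in post-menarchal participants, run on the urine or blood already collected. It cannot cover imaging done before screening under the 3-month allowance of item 14.
- **Section 3:** have the sponsor state how pregnancy status is handled before any second injection. How that is done is for the sponsor and the clinical team to decide.
- **Section 13.6:** have the sponsor state how a pregnancy during follow-up is reported and followed, so that the birth-defect criterion in 13.1.2 can be applied.

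The cost is one inexpensive test on an existing sample, a few lines of protocol text and added consent wording for adolescents and guardians about the test. Dose, design, endpoints and analysis stay as they are.
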